## Abstract

**Background:**

Physical activity is linked to benefits such as increased physical fitness, cognition, emotional and social functioning, general health and well-being in older people. Some evidence suggests that this also applies to people living with dementia. However, it can be harder for them to perform physical activities, due to several barriers, such as issues with orientation and balance problems. A relatively new type of physical activity called exergaming may help them overcome these barriers. Exergaming is “physical exercise interactively combined with cognitive stimulation in a gaming environment”. The aim of our study is to evaluate the effectiveness and cost-effectiveness of exergaming compared to regular activities in people living with dementia, who attend day-care centres. Additionally, we want to investigate whether the exergaming activity for the person living with dementia, also (indirectly) affects the informal caregiver, as well as which facilitators and barriers to implementation of exergames for this target group exist.

**Methods:**

A cluster Randomized Controlled Trial (RCT), with economic and process evaluations alongside will be carried out. In the Netherlands, 24 day-care centres are randomized in the experimental or control group. The study group will consist of 224 dyads (community-dwelling participants with dementia and their informal caregivers), who are interviewed at baseline, and at 3 and 6 months of follow-up. The participant with dementia has to visit the day-care centre for at least two days per week, have a diagnosis of mild to moderate dementia and have an informal caregiver present, who is willing to participate. Societal cost data will be collected during interviews, using healthcare utilization diaries, and from day-care centres. The process evaluation will only involve the experimental group, and will include an online survey, qualitative interviews and focus groups.

**Discussion:**

This study will contribute to the evidence base that more effective exercise among people with dementia will result in positive effects on their wellbeing and quality of life. This will motivate people with dementia to be physically active. We also envision that there might be a positive effect on the burden of care experienced by their informal caregivers.

**Trial registration:**

This trial was registered at the Netherlands Trial Register (NTR) on December 10, 2015 (number: NTR5537), this publication is based on protocol amendment number 01, issue date 28 December 2018. This includes all items from the World Health Organization Trial Registration Data Set [see Additional file 1].

**Electronic supplementary material:**

The online version of this article (10.1186/s12877-019-1062-x) contains supplementary material, which is available to authorized users.

## Background

Physical inactivity and a sedentary lifestyle are related to negative health-outcomes, such as increased mortality [1–4], reduced well-being and quality of life [5–7], and an increase in health related costs [8, 9]. On the other hand, physical activity is linked to benefits such as increased physical fitness, cognition, emotional and social functioning, and general health and well-being in older people [10–16]. There is some evidence that this also applies for people living with dementia on outcomes like physical, cognitive, emotional and social functioning [17–26]. However, it can be harder for them to participate in physical activity due to several barriers they may experience. For example, orientation (wandering, getting lost) [27] and balance problems (vertigo, risk of falls) [28] can make it more challenging for people living with dementia to engage safely in physical activities outside the house. Other examples of barriers are a decrease of initiative and interest (increase of apathy) [29, 30], as well as various psychosocial issues (i.e. negative attitudes toward exercise, lack of perceived behaviour control) [31].

A relatively new type of physical activity called exergaming may help people living with dementia overcome barriers they experience with regard to physical activities [32]. Our definition of exergaming is “physical exercise interactively combined with cognitive stimulation in a gaming environment” [33, 34]. Technology registers the movements of the participant, which influence the course of a game on a screen [35]. There are various exergaming applications, such as games that are interactively connected to motion sensing devices (e.g., *“Kinect©”*, “*Wii Fit©”,* and “*PlayStation©*” games with sports). Other applications are interactive walking or cycling, with a treadmill or a stationary bicycle connected to a screen, on which digital video images of the environment are shown. The participants can pick a route and by their walking or cycling pace adjust the speed of the film [33].

Exergaming is expected to be a joyful activity in itself for people with dementia and, thus, a feasible way to motivate them to engage in physical activities in a safe manner [36–39]. International studies which included people living with dementia show some promising effects of exergaming, for example that it can improve physical [40, 41], cognitive [38, 40] and emotional functioning [41]. Small-scale pilots in Dutch psychogeriatric day-care centres and nursing homes also yielded encouraging results [32, 42, 43]. Moreover, exergaming motivated older people with dementia to exercise longer and the videos sometimes evoked memories, which led to mental activation [42]. Additionally, it was relatively easier for staff to get people with dementia involved in physical activities, because they were motivated to exercise [42]. However, more robust research studies are needed to investigate the effects of exergaming in comparison with the physical activities people normally perform in their daily lives [33]. Furthermore, there is also a lack of research into exergaming for people living with dementia on the effects of informal caregivers, as well as on cost-effectiveness and implementation [33].

This article describes the design of a cluster Randomized Controlled Trial (RCT) and process evaluation that intends to contribute to the evidence base for the effect of exergames on physical activity in people with dementia. The aim of our study is to investigate the effectiveness and cost-effectiveness of exergaming compared to regular activities in people living with dementia, who attend day-care centres. Additionally, we want to investigate whether the exergaming activity for the person living with dementia, also (indirectly) affects the informal caregiver, in regard to quality of life, experienced burden and positive care experiences.

We theorize that exergaming has a positive effect on several domains of quality of life of people living with dementia and their informal caregivers [44]. The physical exercise involved in exergaming may promote physical fitness, as well as the physical and emotional functioning of the person living with dementia. Additionally, through the interaction with the game on a screen the cognitive and emotional functioning of the person living with dementia might be influenced positively. Moreover, the social engagement involved in participating in the exergaming activity in a day-care centre (e.g., by cycling together or interacting with spectators) may positively affect social functioning. For informal caregivers, we expect that they will find it reassuring to know that the person with dementia is engaged in a meaningful activity, that they can talk about afterwards. Moreover, the informal caregivers may notice a positive change in the behaviour of the person with dementia, because they have been engaged in a fun activity. This may contribute to positive care experiences of the informal caregivers as well as a reduction in the experienced burden of the informal caregiver. Taking into account all these factors we expect that exergaming will have a positive effect on the quality of life of both the person with dementia and the informal caregiver.

The objectives of our study are to conduct:An effect evaluation to determine whether:persons with dementia in day-care centres with exergaming are more physically active and have improved mobility compared to persons with dementia in day-care centres without exergaming;exergaming has a positive effect on the physical, cognitive, emotional and social functioning and the quality of life of people with dementia. in comparison to regular activities offered in day-care centres;exergaming has an effect on quality of life, experienced burden and positive care experiences of the informal caregivers;exergaming is cost-effective from a societal perspective in comparison to regular activities in day-care centres for people with dementia and their informal caregivers.A process evaluation to determine:whether people with dementia (in the exergaming group) enjoy the exergaming activity and whether this is related to characteristics of the participant or the context;facilitators and barriers to implementation of exergames for community-dwelling people living with dementia;how people living with dementia, informal caregivers, staff of day-care centres and companies developing exergames think we can best apply the exergaming intervention for people with dementia;how well exergaming was executed in the day centres during the RCT and whether care professionals saw benefits in its use.

## Methods

### Study design and setting

We will study the effectiveness and cost-effectiveness of exergaming in a cluster RCT using a randomized controlled block design. All aspects of this trial (design, conduct, and reporting) will adhere to the requirements of the SPIRIT statement (Standard Protocol Items: Recommendations for Interventional Trials) [45, 46] as well as to the Consolidation Standards of Reporting Trials (CONSORT) guidelines [47]. A completed SPIRIT checklist of our trial protocol is available upon request. We will compare people with dementia (and their informal caregivers), who visit day-care centres which offer exergaming to people with dementia (and their informal caregivers), who visit day-care centres that offer regular activities regarding the following outcome variables: physical activity, mobility and physical, cognitive, emotional and social functioning, quality of life of people with dementia and their informal caregivers, experienced burden and positive care experiences of the informal caregivers, and societal costs. The comparator of regular activities at day-care centres without exergaming has been chosen, to ensure that any between-group effect we will find, can be contributed to the exergaming intervention.

Interviews and tests will be scheduled at the start of the study (baseline), after three and after 6 months (two follow up measurements). In total, 24 day-care centres will be recruited. All day-care centres are located in the Netherlands, there are no restrictions to which parts of the country. A list of the study sites will be available upon request. The process analysis will only be carried out in the experimental group.

### Recruitment and randomization day-care centres

An overview of the recruitment and randomization process for the day-care centres can be found in Fig. 1.

**Fig. 1 Fig1:**
[figure not shown]
Flow chart of the randomization of day-care centres

We will (if possible) arrange blocks of centres that are similar to one another (in terms of region and/or target group: i.e. severity of dementia, age of onset, ethnicity, group size in the day-care centre). This is to control for environmental factors that might possibly influence the outcomes. Within these blocks, day-care centres will be randomized by an independent researcher, using Random Allocation Software [48], to either the experimental (exergaming) group or control (regular activities) group (12 day-care centres per group). After randomization, the day-care centres will remain in the experimental or control group throughout the duration of the trial.

Day-care centres which already have the required exergaming equipment, will be paired up with a comparable day-care centre from the same or another care organization without the equipment. Then they will be randomized as a pair instead of as an individual day-care centre. If this pair is randomized in the experimental group, the day-care centre with the exergaming equipment will participate in the trial. Similarly, if this pair is randomized in the control group, the day-care centre without the equipment will participate in the trial. Day-care centres which do not have any exergaming equipment yet, can also be enrolled for randomization individually if they are willing and able to buy the exergaming equipment needed for the trial. This has to be confirmed, prior to randomization, and is intended to ensure they can still participate when they are randomized to the experimental group.

Day-care centres in both groups will each receive an allowance of at most € 1.125,-. When they recruit eight persons or more. They can decide themselves how they want to spend this, for example to pay their staff for the extra hours they have to put in to participate in the research project. Day-care centres in the experimental group may also put this amount towards the purchase of the exergaming equipment.

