### Participants and setting

An overview of the recruitment and participant timeline can be found in Fig. 2. In this RCT, dyads will participate each consisting of a person living with dementia, who attends a day-care centre and his or her informal caregiver. Participants with dementia can be either existing or new visitors of a day-care centre in the Netherlands.

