#### Secondary outcome measures

##### Economic evaluation

The economic evaluation will be performed from a societal perspective. Healthcare utilization and informal care will be measured using cost diaries, and costs will be calculated according to the Dutch guidelines for economic evaluations [56]. Costs of the exergaming intervention are calculated using a bottom-up approach based on information with interviews with staff members at the day-care centre using the form ‘Costs and benefits of applied games’ [35]. Quality of life will be measured using the three-level version of the EuroQol questionnaire (EQ-5D-5 L) [57]. EQ-5D-5 L health states will be converted to utility scores using the Dutch EQ-5D-5 L tariff [58]. The utility scores will be used to calculate Quality-Adjusted Life-Years (QALYs) using the area-under-the-curve method. The secondary outcomes can be found in Tables 2, 3, and 4.

**Table 2 Tab2:** Secondary outcome measures for participants living with dementia

Outcome	Outcome measure	Recorded by	Timing		
			Baseline	3 months	6 months
Physical functioning	Physical Activity Scale of the Elderly (PASE) [67]	Researcher during interview	X	X	X
Cognitive functioning	Mini-Mental State Examination (MMSE) [68, 69]	Researcher by means of test	X	X	X
Cognitive functioning	Trail Making Test (TMT) [70]	Researcher by means of test	X	X	X
Social functioning	One question from the Adult Social Care Outcomes Toolkit (ASCOT) [71]	Researcher during interview	X	X	X
- Demographics and personal characteristics - Physical functioning - Cognitive functioning - Social functioning - Emotional functioning - Quality of life	The Older Persons and Informal Caregivers Survey Minimum DataSet (TOPICS-MDS care recipient) [72], including EuroQol five dimensions questionnaire with five-level scale (EQ-5D-5 L) [73, 74]	Researcher during interview	X	X	X
Interest in and enjoyment of physical exercise	Intrinsic Motivation Inventory (IMI) [66]	Researcher during interview	X	X	X
Satisfaction with the exergaming activity (*only experimental group*)	Separate questions	Researcher during interview	X	X	X
Body Mass Index (BMI)	Weight scale and measuring tape to measure height	Researcher during interview	X

**Table 3 Tab3:** Secondary outcome measures for informal caregivers

Outcome	Outcome measure	Recorded by	Timing			
			Baseline	3 months	6 months	0–6 months (ongoing)

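### In the paired enrolment route, prior equipment ownership and trial arm coincide, so randomisation does not balance differences between pair members and does not by itself secure attribution of the effect to exergaming

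*Protocol article*

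**What the plan says.** The section on recruitment and randomisation of day-care centres describes two ways into the trial.

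- **Paired route.** A centre that already has the equipment "will be paired up with a comparable day-care centre from the same or another care organization without the equipment". The unit of randomisation is then the pair and not the single centre. Which member enters depends on the result: "If this pair is randomized in the experimental group, the day-care centre with the exergaming equipment will participate in the trial", whereas "if this pair is randomized in the control group, the day-care centre without the equipment will participate in the trial".
- **Individual route.** Centres without equipment "can also be enrolled for randomization individually if they are willing and able to buy the exergaming equipment needed for the trial".

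Blocks are formed where possible on region and/or target group. Prior ownership is not among the listed features.

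Study design and setting says the comparator was chosen "to ensure that any between-group effect we will find, can be contributed to the exergaming intervention". Participants and setting adds: "Participants with dementia can be either existing or new visitors of a day-care centre in the Netherlands". Under Primary outcome measures, physical activity is registered at baseline, 3 and 6 months, and exergaming counts towards it. The Effect evaluation section gives examples of potential confounders: type of exergaming equipment, amount of staff support and severity of dementia. Prior ownership is not named.

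**The concern.** In an ordinary cluster trial, allocation decides which treatment a given centre delivers, so the arms differ only by chance in everything else. In the paired route it decides which of two different centres is observed. The owner is never seen under control, and its partner is never seen under exergaming. The arm difference in these slots is therefore the effect of exergaming plus whatever separates owners from their partners.

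A second problem follows. If existing visitors of an owner centre were already using the equipment, their baseline physical activity may include the intervention and so may not be a pre-exposure value.

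At stake is whether the main between-group comparison rests on randomisation throughout, as the attribution sentence implies, or only in part.

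**Working it through.** **1. What each route compares.** Write Y(1) and Y(0) for a centre's mean outcome with and without exergaming.

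- Individual route: expected arm difference = E[Y(1)] − E[Y(0)] over the same population of centres, which is the effect.
- Paired route: expected arm difference = E[Y_owner(1)] − E[Y_partner(0)] = E[Y_owner(1) − Y_owner(0)] + E[Y_owner(0) − Y_partner(0)] = effect in owners + g.

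Here g is the within-pair gap in the absence of exergaming. Features common to both members cancel from g. Features that differ do not.

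**2. Can adjustment remove g?** Not through ownership. In the paired route every experimental centre is an owner and every control centre is not, so an ownership term is collinear with arm. Type of exergaming equipment, the nearest listed confounder, has no value in controls. Adjusting for measured proxies such as staff support or severity can remove only the part of g that they carry.

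**3. Pooled size.** Let p of the 24 randomised units be pairs. With 12 units per arm, the expected number of owners in the experimental arm is p × 12/24 = p/2, a share of (p/2)/12 = p/24. The share in the control arm is 0. Pooled bias = g × p/24.

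The protocol gives neither p nor g. Purely as an illustration, the table assumes no true effect, 9 dyads per centre, the protocol's ICC of 0.05 and SD of 4.6, and a t-test on centre means (10,000 simulated trials per p). MMSE is used because it is the only outcome with planning figures; it is a secondary outcome.

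| Pairs p | Owner share, experimental arm | Bias if g = 0.5 points | Bias if g = 2 points | Type I error, g = 0.5 | Type I error, g = 2 |
|---|---|---|---|---|---|
| 2 | 8% | 0.04 | 0.17 | 0.05 | 0.05 |
| 4 | 17% | 0.08 | 0.33 | 0.05 | 0.07 |
| 6 | 25% | 0.13 | 0.50 | 0.06 | 0.09 |
| 8 | 33% | 0.17 | 0.67 | 0.06 | 0.12 |
| 12 | 50% | 0.25 | 1.00 | 0.06 | 0.22 |

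With g = 0 the simulated rate was 0.047 to 0.055, so small departures from 0.05 are noise. A gap of 2 points equals the whole planned effect and is an extreme assumption.

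**4. Cost of restricting to individually randomised centres.** First the plan's own figure, from Sample size calculation (difference 2, SD 4.6, 80% power, alpha 0.05 taken as two-sided, ICC 0.05, 7 dyads per cluster, 4% drop-out):

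- Total before clustering = 4 × (1.960 + 0.842)² × (4.6/2)² = 166.1; the plan says 166.
- Design effect = 1 + (7 − 1) × 0.05 = 1.30.
- 166 × 1.30 / 0.96 = 224.8; the plan says 224. The figure reproduces to within rounding.

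Without the pairs, analysed dyads = (24 − p) × (224/24) × 0.96, and effective size per arm = that / 1.30 / 2, assuming the remaining centres split equally.

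| p | Analysed dyads | Power |
|---|---|---|
| 0 | 215.0 | 80% |
| 2 | 197.1 | 76% |
| 4 | 179.2 | 72% |
| 6 | 161.3 | 68% |
| 8 | 143.4 | 63% |
| 12 | 107.5 | 51% |

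The plan's 24 centres and 224 dyads imply 224/24 = 9.3 per centre. That would give a larger design effect than 1.30 and somewhat lower powers.

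**5. Baseline exposure.** Eligible existing visitors, plus a primary outcome that counts exergaming at baseline, mean that pre-trial use at owner centres would enter the baseline value. With change scores, or with baseline activity kept as a confounder, this would tend to understate the effect on activity. Without either, an owner centre that was already more active would tend to inflate it. The Effect evaluation section describes mixed models with confounders chosen from baseline differences and does not fix a change-score analysis, so no direction follows.

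**The case against.** The strongest defence is that the protocol anticipated the difficulty. It openly describes both routes, asks for a comparable partner (possibly from the same care organisation), randomises the pair, and blocks where it can on region and target group. Exergaming is recorded at baseline, past experience with cycling, technology and games is collected, and staff support and severity are candidate confounders. The attribution sentence explains the choice of comparator and is not about pairing. A sensitivity analysis by route is ordinary SAP content, and the SAP is not shown.

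Much of this stands, and it rules out several stronger readings that a reader might infer:

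- *Randomisation gives no balance at all.* Not supported. What the pair members share is balanced in expectation; only differences within pairs are unprotected.
- *The protocol conceals the mixture of routes.* It does not.
- *The bias is a definite fraction of the planned effect.* For example, a pair share of 25–75% and a gap of 0.2 SD would give 0.05–0.15 SD, or 12–35% of 2/4.6 = 0.435 SD. Both inputs are assumptions, and the benchmark is the MMSE, not a primary outcome.
- *Baseline use pulls the effect towards zero.* The direction is not established.
- *Table 2 shows prior use at owner centres.* The row "Satisfaction with the exergaming activity" has a baseline mark, but it covers the whole experimental group and does not single out owners.

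What the defence does not answer is the rule itself. No criteria for a comparable partner are stated. The willingness-to-buy condition is attached only to individual enrolment. Ownership cannot be adjusted for. The objection here is to a stated allocation rule and a stated claim, not to detail left for an SAP.

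**Conclusion.** The point holds for the paired slots. There, ownership and arm coincide whatever the number of pairs, differences between pair members rest on unspecified matching, and attribution to exergaming is not secured by randomisation. Some participants' baseline may also not be pre-exposure. Individually enrolled centres are unaffected by this mechanism.

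The structural conclusion needs no numerical assumption. The size does: it is pair share times gap, and the document supplies neither. The tables show only how the answer moves. With few pairs or a small gap the consequence is negligible; with half the units paired and a gap as large as the planned MMSE effect it would be serious.

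**What to change.** Trial status reports that recruitment of centres and participants was complete and data collection still running at initial submission, so the remedy lies in analysis and reporting, fixed before results are seen.

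1. Record the enrolment route (paired or individual) for every centre, and report the number of pairs.
2. Keep the all-centre analysis as the main one.
3. Pre-specify beside it a sensitivity analysis limited to individually randomised centres, and show the effect by route.
4. Report baseline exergaming use by arm and route. Do not exclude prior users: at owner centres they occur only in the experimental arm, so removing them would create a new selection difference.
5. Qualify the attribution sentence in Study design and setting: for paired slots, attribution also depends on the comparability of the pair members.

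The cost is one additional analysis, a route variable that should be recoverable from the randomisation records, and a narrower claim. The restricted analysis has lower power (about 76% with 2 pairs, 51% with 12), which is why it should accompany the all-centre result and not replace it. It removes only the ownership problem. Recruitment by unblinded centre staff, which the Discussion expects to be harder in control centres, affects both routes.
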